### Participant adherence and compliance

Participants will be allowed to withdraw at any time; nevertheless, several strategies will be used for adherence and compliance with the intervention. The minimum compliance allowed at each phase of the intervention will be 50% but the overall compliance after 9 months will have to reach 70%. A lack of compliance (< 50%) without justified reasons in the first phase of the intervention will result in the participant being invited to drop out from the study. This 70% adherence rate means completing 95 sessions of 136. If a participant has not completed 70% of the intervention by the end of the 9 months but can reach 70% within two additional weeks, the exercise programme will be extended for them. Compliance with the intervention will be monitored using a diary and it will be sent to the research staff on a monthly basis (Item 5). Parental involvement will be requested for this matter.

Participants and their parents are verbally motivated to participate in the intervention and to attend to all the assessments. Children who complete successfully the intervention will get a certificate of achievement. Children are the key part of this study and they deserve acknowledgements for their positive attitude and willingness (and their family) to participate in this study.

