**Methods:**

A minimum of 116 participants aged 6 to 18 years will be randomized into an intervention (*n* = 58) or control group (*n* = 58). The intervention group will receive an online exercise programme and diet counselling on calcium and vitamin D. In addition, five behaviour change techniques and a gamification design will be implemented in order to increase the interest of this non-game programme. The control group will only receive diet counselling. Participants will be assessed on 3 occasions: 1) at baseline; 2) after the 9 months of the intervention; 3) 4 months following the intervention. The primary outcome will be determined by dual energy X-ray absorptiometry (DXA) and the hip structural analysis, trabecular bone score and 3D-DXA softwares. Secondary outcomes will include anthropometry, body composition, physical fitness, physical activity, calcium and vitamin D intake, blood samples, quality of life and mental health.

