### Statistical analysis

All variables will be checked for normality using both statistical and graphical methods. Results will be presented as frequencies and proportions with 95% confidence intervals for categorical variables and mean (standard deviation) or median (range) for continuous variables. A descriptive analysis of the participants characteristics will be performed as soon as the baseline assessments are completed. This cross-sectional analysis will show the comparability of IG and CG and the need for adjustment when between group comparisons are done.

General Lineal Models will be used to examine the training effects [time (pre-post 9-month intervention) x group interaction] on the primary and secondary outcomes. Change in bone outcomes will be used as age and sex-adjusted z-scores. The baseline level of each outcome variable will be entered as covariate. Effect sizes will be reported. Multiple imputation methods and sensitivity analysis (i.e. propensity score) will be performed to handle missing data and appreciate the potential influence of missing responses. Finally, in the event of possible dropouts, a statistical analysis will be carried out by protocol and intention to treat.

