#### Periodisation

Although Peitz et al. [59] did not find differences between no, linear and undulating periodisations in youth, iBoneFIT will implement a linear model based on the fact that variation in volume and/or impact loading within the programme phases may stimulate greater bone adaptions and reduce boredom and risk of over-training [44]. The exercise programme will be divided in three phases of different durations and impact loadings (i.e. height reached in the different jumps). Each phase will be composed of levels with progressive increase in volume (i.e. repetitions, sets per day and sessions per week) as shown in Table 3 (Item 7b).

The phase 1 corresponds to the first 8 weeks of the exercise programme. Participants will perform body mass-based squats and the volume will increase progressively by modifying the number of repetitions and sets per day. Paediatric cancer survivors may present reduced aBMD and muscular fitness [60], therefore jumping exercise prescription may not be safe. In this sense, body mass-based squat was chosen in this phase following previous studies that observed positive effects on muscular fitness after an 8-week intervention [61, 62].

The phase 2 will last 12 weeks and participants will perform squat jumps. In this phase, the volume will increase progressively by modifying the number of repetitions, sets per day and sessions per week. Squat jump has been chosen as intermediary exercise before the use of countermovement jump since the jump height reached is lower and hence, ground reaction forces produced at the landing are lower [63]. Furthermore, squat jump training reduces the degree of muscle slack on the push-off phase [64] which could supply a better execution of the countermovement jump afterwards.

The phase 3 will be the longest phase of the exercise programme with 16 weeks. Participants will perform countermovement jumps and the volume of this phase will be increased progressively by modifying the number of repetitions, sets per day and sessions per week. Countermovement jump will be chosen in this phase since it produces a huge force application (~ 400 times body mass / second) and ground reaction forces (~ 5 times body mass) in youth [65, 66]. Countermovement jump has been previously reported to be valid and reliable in children [67].

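### The low-adherence rule asks exercise-arm children to leave the study, not just the programme, so outcomes can be lost in one arm because of post-randomisation adherence

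*Protocol article*

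**What the plan says.** All references are to the Protocol article.

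- **Participant adherence and compliance** sets a floor of 50% for each phase and 70% overall. Its consequence for an early shortfall is that unexcused compliance below 50% in phase 1 "will result in the participant being invited to drop out from the study". The object is the study, not the exercise programme. No such consequence is attached to phases 2 and 3.
- Compliance is measured in exercise sessions: "This 70% adherence rate means completing 95 sessions of 136".
- **Abstract, Methods**, on the comparator: "The control group will only receive diet counselling". The Control group section agrees; controls have no sessions to complete.
- **Periodisation**: "The phase 1 corresponds to the first 8 weeks of the exercise programme".
- **Statistical analysis**, on analysis sets: "in the event of possible dropouts, a statistical analysis will be carried out by protocol and intention to treat". Neither set is named as primary. On missing data: "Multiple imputation methods and sensitivity analysis (i.e. propensity score) will be performed to handle missing data".

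The article does not say that children who leave under the rule are still measured at T1 (9 months) or T2 (13 months).

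**The concern.** An intention-to-treat comparison needs outcomes from the children as randomised. Here a written rule asks some of them to leave because of what they did after randomisation, and it can reach only the exercise arm. A control child with equally low motivation or habitual activity stays and is measured. If low adherers would have gained less bone anyway, or gain less because they did not exercise, their absence raises the exercise-arm mean.

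The planned remedies do not clearly repair this. Standard multiple imputation and propensity methods rely on the observed data explaining the missingness. Phase 1 compliance is recorded by diary, so an imputation model could include it. But if the rule is followed, few or no children below the threshold will have a T1 outcome, so the model must extrapolate below 50% from children above it. The data could not test that extrapolation. At stake is whether the primary comparison estimates the effect of offering the programme.

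**Working it through.** **1. The plan's own figures.** Table 3 has nine levels of 4 weeks: 4 × (4+4+3+4+4+3+4+4+4) = 4 × 34 = 136 sessions, as stated. 0.70 × 136 = 95.2, so 95 sessions agrees after rounding. Phase 1 is 8 weeks × 4 sessions = 32 sessions, and 50% is 16, so the rule applies to fewer than 16 completed sessions.

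**2. Inputs.** From the article: 58 children per arm, two arms, a rule on sessions that only one arm has. Not in the article, hence assumed: the share *q* of the exercise arm that leaves (10–20%) and the correlation *c* between adherence and bone change (0.1–0.4).

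**3. Shift in the exercise-arm mean with no true effect.** If adherence and change are jointly normal and the lowest share *q* of adherers is lost, the retained mean moves up by

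shift = *c* × φ(z_q) / (1 − *q*), in SD of change.

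With equal SDs, SE = √(1/n + 1/58), where n is the number of exercise-arm children left. The rejection rate is that of a two-sided 5% t test with noncentrality shift/SE.

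| q | c | φ(z_q)/(1−q) | shift | n | SE | shift/SE | type I error |
|---|---|---|---|---|---|---|---|
| 0.10 | 0.1 | 0.1755/0.90 = 0.195 | 0.02 | 52 | 0.191 | 0.10 | 5.1% |
| 0.15 | 0.3 | 0.2332/0.85 = 0.274 | 0.08 | 49 | 0.194 | 0.42 | 7.1% |
| 0.20 | 0.4 | 0.2800/0.80 = 0.350 | 0.14 | 46 | 0.197 | 0.71 | 10.8% |

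The model supposes that everyone in the low tail leaves. The rule is voluntary and excuses some, so for a given *q* these shifts are towards the upper side.

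**4. A second route, with a true effect.** Let *D* be the effect in those who stay, *k* the fraction of it gained by those who leave, and *g* how much worse (in SD) the leavers would have done without exercise.

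ITT effect = *D* × [1 − *q*(1 − *k*)]

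Bias of the completer estimate = *q*(1 − *k*)*D* + *q g*

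Take *q* = 0.20, *D* = 0.25, *k* = 0, *g* = 0.5, all illustrative. The ITT effect is 0.25 × 0.80 = 0.20 and the bias is 0.05 + 0.10 = 0.15. A simulation (58 per arm, baseline-adjusted, baseline–outcome correlation 0.7, 1,500 runs, 10 imputations) gave 0.194 when all children were measured, 0.343 for completers and 0.343 after imputation from arm and baseline. Imputation of that kind returned the completer answer. This scale is not the SD of change used in step 3.

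With no true effect and *g* = 0.5, simulated type I error after imputation was 6.8% at 10% removed and 9.4% at 20%, against 4.8% in both cases when every child was measured.

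**5. Direction.** The bias is zero if *D* = 0 and *g* = 0. It reverses if leavers would have done sufficiently better: with *q* = 0.20, *D* = 0.25, *k* = 0 and *g* = −0.5, it is 0.05 − 0.10 = −0.05.

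**The case against.** The rule is narrower than it may seem, and much of the case on the other side stands.

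- It covers only unexcused low compliance, and the child is asked, not required, to leave. The article does not define an acceptable reason, but illness or injury would probably qualify, which weakens the route to bias through poor health. Motivation and habitual activity remain.
- A reader might infer that the trial becomes adherent exercisers against all controls. The article does not support that. Children at or above 50% in phase 1, those with an accepted reason, those who decline to leave, and those whose adherence falls in phases 2 and 3 can all stay. The retained arm will include poor adherers in the jumping phases.
- A reader might also infer that the result is certainly biased towards exercise. Step 5 shows that this is likely, not certain.
- Every size above rests on assumed rates. At the low end (0.02 SD) the effect on the error rate is negligible.
- The plan commits to an intention-to-treat analysis, and children and parents are encouraged to attend every assessment. Imputation details may properly sit in an analysis plan that is not shown.

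The last point softens the concern without resolving it. No sentence extends later assessments to children who leave under the rule, and an intention-to-treat label cannot supply outcomes that were not collected.

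**Conclusion.** The point holds in limited form. As written, the rule can remove outcomes from the exercise arm only, on the basis of adherence after randomisation, and it works against the intention-to-treat analysis that the same article promises. Imputation would rest on extrapolation from better adherers.

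The bias probably favours exercise; its direction is not certain and its size cannot be known from the article. Under assumed removal of 10–20% and adherence-outcome correlations of 0.1–0.4, it is about 0.02–0.14 SD of change with a type I error of roughly 5–11%. The case for changing the rule does not depend on those figures: outcomes not collected cannot be recovered, and the change is cheap.

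**What to change.** Amend the section on participant adherence and compliance to separate stopping the programme from leaving the study. Low adherence should never end study participation: a child who stops the programme is still invited to T1 and T2 and is analysed in the arm to which they were randomised. This leaves open how low adherence to the exercise programme itself is managed.

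In the statistical analysis section, name intention to treat as the primary analysis and per protocol as supportive. For exercise-arm children who still miss T1, add a control-based or delta-adjusted multiple imputation sensitivity analysis. It should stand beside the planned propensity-score analysis, not replace it.

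The cost is a short amendment, a few assessment visits that were already planned for these children, and an effect estimate diluted by non-adherence, which is what an estimate of offering the programme should reflect.

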### Intervention

#### Exercise programme rationale

The rationale of the iBoneFIT exercise programme will be described following the Consensus on Exercise Reporting Template (CERT) criteria recommendations [46]. The items detailing the recommendations are shown in Table 1.

**Table 1 Tab1:** CERT checklist from iBoneFIT study exercise programme

Item	Checklist item	Identification (section)
1	Detailed description of exercise equipment	Exercise programme characteristics
2	Detailed description of the qualifications, expertise and/or training	Exercise programme characteristics
3	Describe whether exercises are performed individually or in a group	Exercise programme characteristics
4	Describe whether exercises are supervised or unsupervised; how they are delivered	Exercise programme characteristics
5	Detailed description of how adherence to exercise is measured and reported	Participant adherence and compliance
6	Detailed description of motivation strategies	Exercise programme characteristics
7a	Detailed description of the description rule(s) determining exercise progression	Exercise programme rationale
7b	Detailed description of how the exercise programme was progressed	Periodisation
8	Detailed description of each exercise to enable replication	Session structure
9	Detailed description of any home programme component	Exercise programme rationale
10	Describe whether there are any non-exercise components	Control group
11	Describe the type and number of adverse events that occur during exercise	Exercise programme characteristics
12	Describe the setting in which the exercises are performed	Exercise programme characteristics
13	Detailed description of the exercise intervention	Intervention
14a	Describe whether the exercises are generic (one size fits all) or tailored	Exercise programme characteristics
14b	Detailed description of how exercises are tailored to the individual	Exercise programme characteristics
15	Describe the decision rule for determining the starting level	Exercise programme rationale
16a	Describe how adherence or fidelity is assessed/measured	Participant adherence and compliance
16b	Describe the extent to which intervention was delivered as planned	Participant adherence and compliance

Since plyometric jump training has been shown to be effective in improving bone health and to maintain the benefits after the intervention in children and adolescents [35], jumping exercise will be the basis for the specific exercise type in iBoneFIT. Notwithstanding, the Exercise Guidelines for Cancer Survivors recommend an extended phase of resistance training before progressing to impact loading [44]. In this sense, a recent systematic review highlighted that resistance training should be incorporated at an early age and prior to plyometric training in order to establish an adequate foundation of strength for power training activities [47]. Therefore, all participants will start with a familiarisation phase aimed to improve muscular fitness before implementing mechanical loading through jumps (Item 7a and 15).

Although the duration of the jumping interventions to be effective on bone outcomes in children and adolescents is unclear, the length of the exercise programme will be 9 months based on results from previous studies [38, 48]. In addition, we have considered the fact that bone remodelling process requires approximately 5 months [49]. Dietary counselling on calcium and vitamin D will be provided to the participants in both control and intervention groups due to having an adequate calcium and vitamin D levels is important as both interact with physical activity to enhance bone mass (Item 9) [28, 50].

#### Exercise programme characteristics

This home-based intervention will be delivered online by making use of social media (Item 4 and 12). Using popular existing social network sites may address issues of reach, engagement, and retention [51, 52]. WhatsApp (WhatsApp Inc., Mountain View, CA, USA) is a highly used app in Spain for social networking and that allows us to send text messages and other types of media (e.g. photos and videos) to the parents of participants. Although WhatsApp has been revealed as a feasible method to deliver exercise interventions, Muntaner-Mas et al. [53] have suggested that the implementation of behaviour change techniques could increment the effectiveness on the outcomes assessed. Thus, five behaviour change techniques (i.e. action planning and goal setting, providing instructions and demonstrations of how to perform the behaviour, self-monitoring of behaviour, providing feedback on performance and information about health consequences) and a gamification design (i.e. points and rankings) will be included to improve the interest and incentive of this non-game programme (Table 2) (Item 6). These motivational approaches were chosen because of their known effect on physical fitness [53], physical activity [54] and satisfaction [55]. Moreover, parents will be told to encourage their children to perform the exercise programme in order to increase motivation.

**Table 2 Tab2:** Translation and operationalization of BCTs targeting behaviour determinants into BIT elements

Determinant	BCT	Operationalization	BIT element	Workflow
Perceived behavioural control; Autonomy; Planning; knowledge/awareness	Action planning and goal setting (behaviour)	Inform the participants about the phase of the intervention and goals	WhatsApp group message	Every 2 weeks (Sunday)
Perceived behavioural control; Intentions; Competence; Knowledge/awareness	Provide instructions and demonstrations on how to perform the behaviour	Give instructions and demonstrations about how to perform the training session	Videos with exercise proposals	Every 2 weeks (Sunday)
Perceived behavioural control; Autonomy; Competence; Knowledge/awareness	Prompt self-monitoring of behaviour	Ask the participants to report the intervention compliance	WhatsApp group message	Every 2 weeks (Sunday)
Perceived behavioural control; Relatedness; Competence; Knoledge/awareness	Provide feedback on performance	Inform the participants about their performance in the main exercises (i.e. body mass-based squat, squat jump and countermovement jump)	WhatsApp group message or video	Every 2 weeks (Friday)
Perceived behavioural control; Attitude (beliefs); Knowledge/awareness	Information about health consequences	Present press releases to emphasize the importance of calcium and vitamin D for bone health	WhatsApp group message	At the beginning of each phase (Sunday)

*BCT* behaviour change technique, *BIT* behaviour intervention technology

A personal trainer with a BSc degree in Sport Sciences will develop all the sessions of this programme (Item 2, 14a and 14b). The personal trainer will record 18 exercise sessions and they will be uploaded in a private channel of the YouTube website. Each of them will be repeated over a 2 weeks period. The YouTube platform has been reported to be an educational tool for healthcare conditions among people coping with illness [56]. Every new session for the following 2 weeks will be shared through the WhatsApp group every 2 weeks. Finally, participants will perform the exercise programme individually or accompanied (i.e. with parents or friends) according to their preferences (Item 3) [57]. They will be required to record videos and send through the WhatsApp group in order to supervise the execution of the jumping exercises by the personal trainer. The exercise programme will be performed on a hard surface (Item 1) [58], and participants will be asked to report any pain or injuries at each stage of the intervention (Item 11).

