### Control group

Participants randomly allocated to the CG will receive information on the recommendations of calcium and vitamin D [69]. Educational leaflets and infographics based on the current recommendations [69] will be delivered to the participants at the beginning of the study (Item 10). After finishing the study, they will be offered the same online exercise programme.

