## Outcomes

The primary outcome of our study is bone health. The secondary outcomes include anthropometric measurements, body composition, physical fitness components, free-living physical activity, blood samples, calcium and vitamin D intake, health-related quality of life and mental health. Assessments will be conducted at baseline, repeated at post-test (i.e. after 2 weeks of intervention or control condition at most) and follow up (i.e. after 4 months of intervention or control condition). Participants will be assessed for the post-test and follow up following the order through which they will be tested at baseline, to avoid cofounding by time between baseline and the other assessments.

Data obtained on the assessments will be recorded on a paper print-out and entered into an Excel file for future statistical analysis. Questionnaires will be filled using Google Forms which allows us to record the data without hand-written management. In compliance with the Personal Information Protection Act, the names of all participants will not be disclosed, and an identifier number will be used to identify each participant. All participants will be informed that the clinical data obtained in the trial will be stored in a computer and will be handled with confidentiality.

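### As described, pain and injury are asked about only at the stages of the exercise programme, so the randomised control group supplies no comparable background rate

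*Protocol article*

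**What the plan says.** Under Exercise programme characteristics, the protocol article states that "participants will be asked to report any pain or injuries at each stage of the intervention (Item 11"). The item number points to Table 1 (Exercise programme rationale), where that row reads "Describe the type and number of adverse events that occur during exercise".

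For controls, the Abstract says "The control group will only receive diet counselling". The Control group section says "Participants randomly allocated to the CG will receive information on the recommendations of calcium and vitamin D", and that leaflets and infographics "will be delivered to the participants at the beginning of the study (Item 10"). Neither place describes a question on pain, injury or fracture.

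The Outcomes section states "The primary outcome of our study is bone health". It continues "The secondary outcomes include anthropometric measurements, body composition, physical fitness components, free-living physical activity, blood samples", then names dietary intake, quality of life and mental health. The sections that follow go down to individual questionnaires, and none of them covers pain, injury or fracture. Statistical analysis deals with the primary and secondary outcomes.

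On safety, the Periodisation section notes that survivors may have reduced areal bone mineral density (aBMD) and muscular fitness, "therefore jumping exercise prescription may not be safe", and gives this as the reason for starting with squats. The Background links low aBMD to a higher risk of fracture.

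**The concern.** Children have aches, injuries and occasional fractures without any exercise programme. A count from exercisers alone mixes that background with whatever the programme adds. If exercisers are prompted repeatedly and controls are not, setting the exercisers' count beside spontaneous control reports would also mislead, because asking produces reports.

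The randomised control group is the natural source of the background rate, and as described it is not used for this. The question matters here because the programme includes 5296 jumps done at home and supervised through videos, in a population for whom the article itself raises a bone-safety question. Controls are to be offered the same programme afterwards.

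**Working it through.** The plan gives no figure on harms to reproduce, so the main check is a reading of the text. The arithmetic only shows what symmetric collection could deliver.

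**Who is asked, and when**

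- *Location.* The sentence belongs to the account of how the programme is delivered. The text just before it concerns participants who do the sessions and send videos.
- *Timing.* It refers to the stages of the intervention. Table 3 sets these as three phases of 8, 12 and 16 weeks (8 + 12 + 16 = 36), and they exist only in the exercise arm. The Outcomes section treats intervention and control condition as two separate things, so the wording does not naturally cover controls.
- *Scope.* The checklist item concerns events during exercise, and controls have no programme exercise.
- *Follow-up.* The stages end at week 36. No solicitation is described between the 9-month and 13-month assessments, even for exercisers.
- *Other sections.* Control group, Outcomes and the outcome sub-sections contain no query that would fill the gap.

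**What a one-arm count yields.** Suppose 12 of 58 exercisers report pain or injury. The 12 is an assumption; the 58 comes from Sample size. The proportion is 12/58 = 20.7%, with a 95% CI of 12.3% to 32.8% (Wilson) or 11.2% to 33.4% (exact). With no control proportion collected in the same way, the risk difference is not estimable. More participants would not help.

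**What asking both arms would yield.** With equal true rates p and n per arm, the 95% half-width for the difference is 1.96 × √(2p(1−p)/n). The calculation uses n = 58, and n = 46 after a 20% loss (58 × 0.8 = 46.4). All rates are assumptions.

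| Rate p in each arm | n = 58 | n = 46 |
|---|---|---|
| 5% | ±7.9 points | ±8.9 points |
| 10% | ±10.9 points | ±12.3 points |
| 20.7% | ±14.7 points | ±16.6 points |

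For the last row at n = 58: 1.96 × √(2 × 0.207 × 0.793/58) = 0.147.

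Power to detect a true increase, two-sided 0.05, is Φ{[(p₂ − p₁) − 1.96√(2p̄(1−p̄)/n)] / √[(p₁(1−p₁) + p₂(1−p₂))/n]}, where p̄ is the mean of p₁ and p₂:

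| Control rate | Doubling, n = 58 | Doubling, n = 46 | Tripling, n = 58 | Tripling, n = 46 |
|---|---|---|---|---|
| 5% | 17% | 15% | 43% | 36% |
| 10% | 32% | 27% | 78% | 67% |
| 20% | 66% | 55% | >99% | 98% |

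Symmetric collection removes the differential asking. It is informative for common events and weak for uncommon ones.

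**The case against.** The strongest reply is that this is a condensed article with no safety section for either arm. The sentence answers an exercise-reporting checklist, so it necessarily speaks of exercisers. A reader might infer that controls will never be asked about harms. No sentence says so, and the full protocol may provide for it. That limit stands, and the point is therefore confined to what the article describes. It is still more than silence: the article does fix how harms are solicited, ties this to programme stages, and gives a detailed list of two-arm measures without a harm item.

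Second, a reader might infer that the article calls these children's bones fragile or concedes that its programme is unsafe. It does neither. The Discussion takes its wording on fragile skeletal sites from guidelines, and the remark on jumping explains the squat phase that precedes it. The remark shows that the authors consider the question live, nothing stronger.

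Third, the trial states no comparative safety aim, and asking exercisers stage by stage serves monitoring. That is fair. Monitoring and comparison are different purposes, and the first is met.

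Fourth, not all harm is invisible: DXA bone measures and the physical-functioning domain of quality of life are taken in both arms. This also stands, and limits the point to reported pain, injury and fracture.

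Finally, Randomization and blinding describes blinding of assessors only. Identical questions would not remove reporting bias from families who know their allocation.

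**Conclusion.** The point holds as a cheap improvement. As described, solicitation of pain and injury follows the exercise programme's stages, and nothing comparable is measured in controls or during the 4-month follow-up. An excess of these events due to the programme therefore cannot be estimated without ascertainment bias.

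The conclusion rests on the article's text and on no numerical assumption. The precision of a remedy does rest on assumption: about ±15 points with 58 per arm and ±17 with 46, at an assumed rate near 21%.

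Two stronger conclusions are not supported. The article does not show that the trial is blind to every kind of harm, since adverse effects on bone measures would appear in both arms. Nor would two-arm questions allow a claim of safety for fracture: at an assumed 5% control rate, power to detect even a doubling is only 15% to 17%.

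**What to change.** Put the same short items on pain, injury and fracture to both arms, with identical wording and recall period, at least at the 9-month and 13-month assessments. Report the proportion by arm and the difference with its 95% CI, as a descriptive safety result and not a powered test. Keep the stage-by-stage reporting in exercisers for monitoring, but base the comparison between arms on the common items only. If the full protocol already does this, one sentence in the article would settle the point.

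The cost is a few items on electronic questionnaires that participants already complete, and a small burden on controls. No extra enrolment is needed. When reporting, state that families know their allocation and that rare events cannot be compared with any precision at this size.
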